**Methods/Design:**

270 people of seventy years and older living at home will be identified in the files of the participating general practitioners. People will be asked to participate when meeting the following inclusion criteria: have experienced a fall in the preceding year or suffer from two of the following risk factors: disturbed balance, mobility problems, dizziness, or the use of benzodiazepines or diuretics. People will be randomly allocated to either the Tai Chi Chuan group (13 weeks, twice a week) or the no treatment control group.

The primary outcome measure is the number of new falls, measured with a diary. The secondary outcome measures are balance, fear of falling, blood pressure, heart rate, lung function parameters, physical activity, functional status, quality of life, mental health, use of walking devices, medication, use of health care services, adjustments to the house, severity of fall incidents and subsequent injuries. Process parameters will be measured to evaluate the Tai Chi Chuan intervention. A cost-effectiveness analysis will be carried out alongside the evaluation of the clinical results. Follow-up measurements will be collected at 3, 6 and 12 months after randomization.

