### Sample size and power

The effect of Tai Chi in decreasing fall incidents is conservatively estimated on 25 percent [10]. A power calculation (alpha = 0,05; beta = 0,1; drop out percentage of twenty percent) estimates that 135 participants are needed in each study group. This implies that we intend to enroll 270 participants in total.

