### Outcome measures

The primary outcome measure is new fall accidents. At the end of the baseline measurements participants will receive a fall calendar. They will be asked to fill in daily for a year if they are fallen, nearly fallen or not fallen. A fall is defined as 'an unintentionally coming to rest on the ground, floor, or other lower level'. A near-fall is defined as 'the person seems to fall, but can prevent the fall by catching or leaning on a person or a thing (e.g. a chair, a drawer or a table)' [12].

When a fall or a near-fall is reported people will be asked to give more details (e.g. how it happened, at what time, if they were hurt, if they started to use devices, whether medical care was needed) on an additional standardized form. The forms can be returned in postage free envelopes at the end of each month. If forms are missing or incomplete the research assistant will contact the participant by phone and together they will complete the forms.

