### Statistical analyses

To assess if randomization was successful, descriptive statistics of baseline characteristics will be used. In case clinically relevant baseline differences regarding prognosis of future incidence of falls is present, effect estimates will be adjusted using multivariate analysis.

Dropouts are defined as participants who stop participating during the first three months (i.e. intervention period). Non-compliers are defined as participants who miss more than twenty percent of the lessons.

The analysis will be performed using the intention-to-treat principle, e.g. all patients are included as randomized irrespective of compliance. Missing values are assigned the last available valid score.

We will evaluate the effect of the intervention in reducing the number of fall incidents using the Student's t-test and survival techniques. To analyze the secondary outcome measures the Student's t-test, the Mann-Whitney test or the Chi-square test will be used according to the type of variable.

When drop out is higher than fifteen percent and/or the compliance is lower than seventy percent an additional per-protocol analysis will be carried out. These are restricted to those participants who complied fully with the intervention protocol and outcome measures.

At the end of the analyses the allocation of participants will be disclosed.

A cost-effectiveness analysis will be conducted alongside the analysis of the clinical data.

Direct costs (such as medication, additional therapy, visits to health care providers) as well as indirect costs (such as disability) measured by the EuroQol, will be related to the primary outcome measure (fall incidents).

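### The primary fall outcome is given both a t-test on counts, which takes no account of observed time, and unspecified survival techniques, with no statement of which decides

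*Protocol article*

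**What the plan says.** All references are to the protocol article.

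- Abstract, Methods/Design: "The primary outcome measure is the number of new falls, measured with a diary".
- Outcome measures, on the diary: "They will be asked to fill in daily for a year if they are fallen, nearly fallen or not fallen".
- Statistical analyses, on the primary outcome: "We will evaluate the effect of the intervention in reducing the number of fall incidents using the Student's t-test and survival techniques". Neither method is ranked above the other and no alpha is split. The kind of survival analysis is not named.
- Sample size and power: "A power calculation (alpha = 0,05; beta = 0,1; drop out percentage of twenty percent) estimates that 135 participants are needed in each study group". The calculation is not tied to either test.
- Statistical analyses, on attrition: "Dropouts are defined as participants who stop participating during the first three months (i.e. intervention period"). Everyone is analysed as randomised, and a missing value takes the last valid one. No person-time or exposure adjustment is mentioned.

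**The concern.** Two questions arise.

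**Which result is the trial's result?** The two methods can disagree. A comparison of mean counts addresses the number of falls. A time-to-first-fall analysis, if that is what is meant, ignores every fall after the first. With no order between them, a reader of the final report cannot tell whether the significant one was chosen in advance.

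**Does the t-test compare like with like?** Someone lost in month two can record at most two months of falls, yet enters the comparison on the same footing as someone with a full year. The plan expects 20% dropout and defines dropouts as people who stop in the first quarter of the year. If more of them are in one arm, that arm shows fewer falls for no clinical reason. More losses in the Tai Chi arm would look like benefit.

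**Working it through.** **The plan's own figure.** The 135 per group cannot be reproduced, because no control fall rate or standard deviation is given. It is used here only as the simulated arm size. Nothing below depends on whether 135 is enough.

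**Inputs from the article:** 135 per group, alpha 0.05, 20% dropout, dropouts lost in months 0-3, one-year diary.

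**Assumptions:** gamma-Poisson (negative binomial) falls; dropout at a time spread evenly over months 0-3, with the diary ending then; two-sided tests (the article does not state sidedness). The article gives neither a fall rate nor a dispersion, so ranges are shown.

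**Step 1: bias from unequal follow-up, no true effect.** A dropout contributes on average 1.5/12 = 0.125 year. Mean exposure in an arm with dropout proportion d is (1 − d) + 0.125d.

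- 10% v 30%: 0.90 + 0.0125 = 0.9125 and 0.70 + 0.0375 = 0.7375. The ratio is 0.808, an apparent 19% reduction.
- 15% v 25%: 0.85 + 0.01875 = 0.86875 and 0.75 + 0.03125 = 0.78125. The ratio is 0.899, an apparent 10% reduction.
- 20% v 20%: the ratio is 1, so there is no bias.

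The planning effect is 25%.

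**Step 2: two tests on one outcome.** P(either) = P(t) + P(log-rank) − P(both). Two independent tests would give 1 − 0.95² = 9.75%. These two are positively correlated, so the figure was simulated: t-test on observed counts, log-rank on first fall, 8,000 runs per main null scenario.

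| Dropout by arm | Mean falls/year, dispersion | t-test | log-rank | either | both |
|---|---|---|---|---|---|
| equal | 0.7, 1 | 4.7% | 4.7% | 7.3% | 2.1% |
| equal | 1.0, 1 | 4.4% | 4.6% | 7.6% | 1.4% |
| equal | 1.0, 2 | 5.2% | 5.3% | 8.7% | 1.8% |
| equal | 1.5, 1 | 5.2% | 5.1% | 8.5% | 1.9% |
| 15% v 25% | 1.0, 1 | 8.2% | 5.1% | 11.2% | 2.0% |
| 10% v 30% | 0.7, 1 | 16.7% | 5.1% | 19.6% | 2.2% |
| 10% v 30% | 1.0, 1 | 19.3% | 5.0% | 22.2% | 2.0% |
| 10% v 30% | 1.0, 2 | 15.5% | 5.1% | 18.5% | 2.1% |
| 10% v 30% | 1.5, 1 | 22.5% | 5.0% | 25.4% | 2.1% |

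Over all equal-dropout settings tried (mean 0.7-1.5, dispersion 0.5-3), the t-test gave 4.4-5.4%, either test 7.3-8.8% and both tests 1.4-2.4%. A second simulation (mean 0.75-1.5, dispersion 1-2) agreed. With equal dropout it gave 4-6% for the t-test and 7-9% for either. With 15% v 25% it gave 7-9% and 10-13%, and with 10% v 30% it gave 14-22% and 17-25%.

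**Step 3: candidate repairs** (mean 1.0, dispersion 1; 3,000 runs).

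- Both tests kept at 0.025 each: 4.3% with equal dropout, but 14.1% with 10% v 30%. Splitting alpha does not cure the neglect of observed time.
- One negative binomial test with log observed time as offset: 5.0% with equal dropout and 4.8% with 10% v 30%.
- Power for a rate ratio of 0.75, from a separate run of 1,000 trials with 108 per arm (135 × 0.8): negative binomial 30%, t-test 29%, log-rank 20%. The change costs no power in this case. The low level itself is a sample-size matter outside this point.

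**The case against.** Several stronger readings are tempting, and the article does not support them.

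- *The primary analysis as a whole ignores observed time.* It does not. Survival techniques censor at loss, and the log-rank stayed near 5% throughout. The criticism applies to the t-test only.
- *Either significant test would count as success.* The article does not say so. If both had to be significant, the type I error would be 1.4-2.4%. A ranking could also stand in an analysis plan that is not shown. This stands: the 7-9% depends on the reading. What the article does fix is the pair of methods, one of them a t-test on a count.
- *Skewed counts and frequent fallers invalidate the t-test.* At this size they do not; with equal dropout it holds about 5%.
- *Dropout will be unequal and the fall data will be lost.* Neither is stated. Process evaluation speaks of people stopping the course, which need not mean stopping the diary, and Outcome measures has missing fall forms completed by telephone. If diaries continue, the bias shrinks or disappears. Timing matters too: with losses spread over the whole year (0.5 year each on average), 15% v 25% gives 0.925 v 0.875, an apparent reduction of about 5% rather than 10%. A separate run with 108 per arm and 15% v 25% dropout gave 5.8-6.1% for the t-test over 1,500 trials, within two Monte Carlo standard errors (0.56 points each) of 5%.
- *The t-test's mean difference does not match a relative planning effect.* The article says only: "The effect of Tai Chi in decreasing fall incidents is conservatively estimated on 25 percent". It gives no scale, so that mismatch cannot be shown.

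The last-valid-value rule does not remove the problem. Applied to a cumulative count, it leaves the truncated count as it is.

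Unequal dropout nevertheless remains plausible, since one arm is asked to attend 26 lessons (13 weeks, twice a week) and practise at home while the other receives no added intervention.

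**Conclusion.** The point holds in limited form, as a should-fix. The article assigns two methods to one primary outcome without saying which decides, and one of them takes no account of observed time.

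- If either result may be claimed, the type I error is about 7-9% with equal dropout, against a planned 5%.
- If early dropouts also stop the diary and dropout differs by arm, the t-test alone rejects a true null in about 7-9% of trials at 15% v 25% and about 14-22% at 10% v 30%.
- With equal dropout the t-test alone is sound at about 5%.

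The ambiguity and the t-test's neglect of observed time can be read directly from the article. The sizes rest on assumed fall rates, dispersion and dropout patterns.

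**What to change.** Name one primary analysis that uses person-time. A suitable choice is negative binomial regression of the number of falls, with log observed diary time (randomisation to 12 months or withdrawal from the diary) as offset, reported as a rate ratio with 95% confidence interval. Make the survival analysis supportive and say which it is: time to first fall, or recurrent events with robust standard errors. Do not use a t-test on raw counts as a deciding test. State also whether people who stop the course continue the diary, since that determines how much observed time is lost.

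The offset corrects for unequal exposure. It does not correct for people leaving because of their fall risk, so reasons for leaving should still be reported by arm.

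The cost is analysis wording only: no new data and no change in sample size. Because the analyst is to be masked until the analyses end, the choice can be fixed without knowledge of the results by arm.

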### Baseline measurements

The baseline measurements consist of the following items. Sociodemographic factors (age, gender, ethnicity, marital status, education, composition of household), physical characteristics (e.g. height, weight, acuity of vision), environmental factors (e.g. pets, adjustments to the house), use of walking devices, medication, and use of health care services (e.g. GP, specialist, physiotherapy, home care/district nurse).

At baseline the following secondary outcome measures are measured: Balance (Berg Balance Scale), fear of falling (The Falls Efficacy Scale), physical parameters (blood pressure and heart rate at rest, FEV1 (i.e. forced expiratory volume during the first second) and PEF (i.e. peak expiratory flow)), physical activity (Physical Activity for the Elderly), functional status (Groningen Activity Restriction Scale), quality of life (EuroQol), and mental health (SF-36). For further details see 'Secondary outcome measures'.

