### Follow-up

As shown in table 2 participants will be followed up during twelve months after baseline measurements. At the end of intervention period (i.e. at three month) and twelve months after the baseline measurement all measurements will be performed. At six months only the questionnaire will be send by mail.

**Table 2 T2:** Variables and timing measurements

**Variable**	**Time measured**			
	Baseline	3 months	6 months	12 months

Inclusion and exclusion variables	TQ			
Falls and near-falls	Continuously every day when fall occur			
Severity of fall incidents	Continuously every day when fall occur			
Sociodemografic, physical and environmental factors	WQ			
Balance (Berg Balance Scale)	M	M		M
Fear of falling (Falls Efficacy Scale)	OQ	OQ		OQ
Physical parameters (blood pressure, heart rate, lung function parameters)	M	M		M
Physical activity (Physical Activity Scale for the Elderly)	WQ	WQ	PQ	WQ
Functional status (Groningen Activity Restriction Scale)	WQ	WQ	PQ	WQ
Quality of life (EuroQol)	WQ	WQ	PQ	WQ
Mental health (SF-36)	WQ	WQ	PQ	WQ
Use of walking devices, medication, use of health care services, adjustments to the house	WQ	WQ	PQ	WQ
Compliance to intervention		X		

TQ = telephone questionnaire; WQ = written questionnaire; OQ = oral questionnaire; PQ = written questionnaire send by post; D = diary, by self report, concurrent registration; M = measurement (e.g. by a test); X = reported by teacher

Questionnaires will be checked on missing data and completed with the participants by phone.

In the invitation letter to visit the location for the follow-up measurement at three and twelve months, participants will be asked not to tell the research assistant whether they are allocated to the intervention or the control group. Moreover a reminder sign will be placed on the location. In this way the research assistant will remain masked.

Every effort will be made to keep the loss to follow-up as small as possible. When the questionnaire sent after six months is not received within two weeks, a phone call is made in order to remind the participant.

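### The secondary scales are measured at baseline and two or three times afterwards, but only two-sample tests are named for them: prespecifying adjustment for each scale's own baseline would gain precision at no cost in data

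*Protocol article*

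**What the plan says.** All references are to the protocol article.

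- **Tests named** (Statistical analyses): "To analyze the secondary outcome measures the Student's t-test, the Mann-Whitney test or the Chi-square test will be used", chosen by type of variable. The text does not say whether the tests are run on follow-up values or on changes from baseline, or at which visit.
- **Baseline values** (Baseline measurements): "At baseline the following secondary outcome measures are measured: Balance (Berg Balance Scale), fear of falling (The Falls Efficacy Scale" opens a list that continues with blood pressure, heart rate, FEV1, PEF, physical activity, functional status, quality of life and mental health.
- **Repeat measurements** (Follow-up): "At the end of intervention period (i.e. at three month) and twelve months after the baseline measurement all measurements will be performed". For the visit in between, "At six months only the questionnaire will be send by mail". Table 2 shows what this means by scale. PASE, GARS, EuroQol and SF-36 have three follow-up values. Balance, fear of falling and the physical parameters have two.
- **Adjustment** (Statistical analyses): "In case clinically relevant baseline differences regarding prognosis of future incidence of falls is present, effect estimates will be adjusted using multivariate analysis". The Discussion says only that adjustments follow if they prove necessary.
- **Missing data** (Statistical analyses): "Missing values are assigned the last available valid score".

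**The concern.** The trial collects a baseline value and two or three follow-up values on about ten measures, but as named the tests take no covariate and no repeated measurements. In a randomised comparison, a scale's own baseline is usually the best single predictor of its follow-up value. Leaving it out keeps explainable variation in the error term and leaves any chance baseline difference in the estimate.

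The conditional clause does not fill the gap. Its trigger is prognosis for falls, not the starting level of GARS, SF-36 or FEV1. It acts only after the baseline tables have been inspected, and no threshold is given. Gender and previous fall, the stratification factors in the Randomization section, do not enter the named tests either.

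At stake is the precision of the results on physical and psychological function, which belong to the trial's stated aim. The Sample size and power section makes no calculation for these outcomes.

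**Working it through.** **Figure to reproduce.** There is none. The 135 per group concerns falls, and no SD, target difference or correlation is given for any secondary outcome.

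**Inputs.**
- Evaluable per arm: 135 × 0.8 = 108 (135 and 20% dropout, Sample size and power).
- Correlation r between baseline and follow-up: not in the document; assumed 0.3 to 0.8.
- Equal variance at baseline and follow-up: assumed, needed for the change-score formula.

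**Formulas.** Variance of the difference between arms, relative to a t-test on final scores at one visit:
- final scores: 1
- change scores: 2(1 − r)
- adjusted for baseline (ANCOVA): 1 − r²

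The cut against final scores is therefore r². The cut against change scores is 1 − (1 − r²)/[2(1 − r)] = 1 − (1 + r)/2 = (1 − r)/2. The cut in interval width against final scores is 1 − √(1 − r²).

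| r | Final | Change | Adjusted | Variance cut vs final | Width cut vs final | Variance cut vs change |
|---|---|---|---|---|---|---|
| 0.3 | 1 | 1.40 | 0.91 | 9% | 5% | 35% |
| 0.5 | 1 | 1.00 | 0.75 | 25% | 13% | 25% |
| 0.7 | 1 | 0.60 | 0.51 | 49% | 29% | 15% |
| 0.8 | 1 | 0.40 | 0.36 | 64% | 40% | 10% |

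**Which comparison applies.** The document does not say, so both columns have to be shown. They move in opposite directions. For r below 0.5 the final-score test is the better simple test and the saving against it is r². For r above 0.5 the change-score test is the better one and the saving is (1 − r)/2. Against the better of the two, the saving is 9% at r = 0.3, peaks at 25% at r = 0.5, and is 10% at r = 0.8. It is positive throughout.

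**Power.** With 108 per arm and two-sided 0.05 (the sidedness is assumed; the protocol does not state it), a difference of 0.381 SD has 80% power with a t-test on final scores. With baseline adjustment the power is 83.6% at r = 0.3, 89.9% at r = 0.5 and 97.5% at r = 0.7.

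**Scope.** The arithmetic belongs to a linear model for a continuous outcome at one visit. It does not carry over directly to items compared by Chi-square, such as walking devices or house adjustments. In Table 2, fall severity is recorded as falls occur and has no baseline value.

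**The case against.** The strongest reply is that nothing here is invalid. In a randomised trial a two-sample comparison is unbiased, and this point does not touch its type I error. The outcomes are secondary, and a condensed article commonly leaves model detail to the analysis plan. The first two statements stand and limit the weight of the point. The third stands only in part, because the article does not leave the method open: it names the tests.

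A reader might infer more than the text supports, in three ways.

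- **That the plan ignores baseline at every visit.** Not supported. The tests could be run on change scores, which use the baseline value; the visit is not stated; and a conditional adjustment exists. What can be said is that no adjustment for each scale's own baseline, and no longitudinal model, is prespecified.
- **That a quarter or more of the precision is lost.** Not supported. This needs a final-score test and r of at least 0.5, neither of which the document gives. If change scores are tested, the loss is below a quarter for every r above 0.5. The quarter is also on the variance scale: at r = 0.5 the interval narrows by only 13%.
- **That every secondary interval would narrow.** Not supported, for the reasons of scope given in the working.

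Two cautions about the remedy also stand. Some bounded scales might have been meant for the Mann-Whitney test, so the plan must say which scales are analysed as means. And people living together are allocated to the same group (Randomization); baseline adjustment does not deal with that dependence, which is a separate matter.

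**Conclusion.** The point holds as a recommendation worth adopting, not as an error that undermines the trial. For the continuous scales with a baseline value, the named tests are a less efficient choice than one the collected data already allow, and the conditional clause does not repair this. In large samples baseline adjustment is at least as precise as a final-score or a change-score test, so the direction does not depend on which was meant.

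The size does. It rests on an r that the document does not give, on equal variances for the change-score comparison, and on a linear model. The ranges in the working are therefore illustrations over assumed r, not properties of this trial's scales.

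**What to change.** Replace the sentence on secondary outcomes, for the continuous scales, with a prespecified model:

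- For each scale, use an ANCOVA at a named visit, or a linear mixed model of all its follow-up values (3 and 12 months; also 6 months for PASE, GARS, EuroQol and SF-36).
- Covariates: the scale's own baseline value, gender and previous fall. The mixed model also has arm, time and arm × time.
- Apply the adjustment regardless of observed baseline balance.
- Report adjusted mean differences with 95% confidence intervals at stated visits, and list the scales analysed this way.
- If the mixed model is chosen, it can use the observed values without carrying the last score forward. State the missing-at-random assumption on which this rests.

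Keep the simple tests for outcomes with no baseline value, such as fall severity. Claim no r² gain for categorical items.

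The cost is analysis wording only: no extra data, visits or participants.

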### Secondary outcome measures

- Balance is measured with the Berg Balance Scale. It consists of fourteen items that are scored on a five-points ordinal scale [13-15].

- Fear of falling is measured with the Falls Efficacy Scale [16]. It is an oral questionnaire and consists of ten items scored on a four points scale, ranging from 'not concerned at all' to 'very concerned'. Participants are asked about how concerned they are that they might fall while performing a series of ten tasks of progressive difficulty in the home environment.

- Physical parameters: blood pressure and heart rate in rest, FEV1 (i.e. forced expiratory volume during the first second) and PEF (i.e. peak expiratory flow). The latter two are measured by a spirometer.

- Physical activities are measured with the Physical Activity Scale for the Elderly (PASE) [17,18]. It combines the frequency of leisure, household and occupational activities over the previous seven days.

- Functional status is measured with the Groningen Activity Restriction Scale (GARS), covering activities of daily living (ADL) and instrumental activities of daily living (IADL) [19]. It consists of eighteen items scored on a four points scale.

- Quality of life is measured with the EuroQol EQ 5-D. It will be used in the cost-effectiveness analysis [20-22].

- Mental health is measured with the SF-36 (subscales) [23-26].

- Use of walking devices, medication, use of health care services (e.g. GP, specialist, physiotherapy, home care/district nurse), adjustments to the house.

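### The plan makes the EuroQol, its quality-of-life instrument, the measure of indirect costs, so that cost component has no valid named source and a health effect sits on the cost side

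*Protocol article*

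**What the plan says.** The economic analysis is set out at the end of the Statistical analyses section of the protocol article. It has two cost parts and names one effect.

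- Direct costs: "Direct costs (such as medication, additional therapy, visits to health care providers").
- Indirect costs, and the effect to which both parts are related: "indirect costs (such as disability) measured by the EuroQol, will be related to the primary outcome measure (fall incidents").

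Three other places describe the EuroQol differently.

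- Secondary outcome measures: "Quality of life is measured with the EuroQol EQ 5-D. It will be used in the cost-effectiveness analysis". The section does not say in which role.
- Baseline measurements, in the list of secondary outcomes: "quality of life (EuroQol), and mental health (SF-36").
- Table 2 under Follow-up lists it as "Quality of life (EuroQol"), at baseline and at 3, 6 and 12 months.

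Table 2 also has a separate resource-use row, "Use of walking devices, medication, use of health care services, adjustments to the house", collected at the same four times. It has no row for indirect costs.

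**The concern.** A cost is a quantity of resources or time multiplied by a price. The EQ-5D asks about current health and returns a health profile, which a tariff can turn into a utility. Neither is a quantity of resources, and the article gives no price that would turn one into money. Disability, the article's example of an indirect cost, is a health state. It may cause costs, such as informal care or lost time, but those have to be recorded in their own right.

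Two things are at stake in the economic analysis. First, an analyst who follows the sentence has no valid way to compute indirect costs. Second, a change in health would be counted as a change in cost. The article's Background names disability among the consequences of falls. Part of the benefit of preventing falls could therefore appear in the numerator of a cost-per-fall ratio while the falls themselves stand in the denominator.

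**Working it through.** The article states no cost, utility or cost-effectiveness figure, so there is nothing to reproduce. The check compares the stated roles and asks what each cost part can be computed from.

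**1. Role of the EuroQol, place by place**

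| Place in the article | Role given |
|---|---|
| Baseline measurements | Secondary outcome: quality of life |
| Secondary outcome measures | Quality of life; to be used in the economic analysis, role not stated |
| Table 2 | Quality of life; baseline, 3, 6 and 12 months |
| Statistical analyses | Measure of indirect costs |

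Three places agree on the construct. The fourth assigns a different one, and nothing in the article corrects it.

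**2. What the analysis as written would compute**

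Incremental ratio = (ΔC_direct + ΔC_indirect) / Δfalls.

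- C_direct = Σ (units used × unit price). The units come from the resource-use row of Table 2. The result is in money, so this part can be computed.
- C_indirect is to come from the EQ-5D, which gives a profile or a utility u. A utility has no money unit, so C_direct + u is not a defined sum. Pricing u would make the sum possible, but it would also turn a health effect into a cost.

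**3. Other sources for indirect costs**

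The resource-use row covers walking devices, medication, health care use and house adjustments. The article names no item on lost time, informal care or productivity. Once the EuroQol is removed, indirect costs have no named source.

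**4. Can the EQ-5D serve as an effect on the existing schedule?**

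Yes. With measurements at 0, 3, 6 and 12 months, the intervals are 3/12 = 0.25, 3/12 = 0.25 and 6/12 = 0.5 years. The area under the curve is

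QALY = 0.25(u0 + u3)/2 + 0.25(u3 + u6)/2 + 0.5(u6 + u12)/2 = 0.125·u0 + 0.25·u3 + 0.375·u6 + 0.25·u12.

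The weights sum to 0.125 + 0.25 + 0.375 + 0.25 = 1, as they should for one year. No extra visit or instrument is needed.

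**The case against.** The strongest reply is that this is a wording slip. The sentence may be a compressed way of saying that costs, and also quality of life as measured by the EuroQol, will be related to falls. That would fit the Secondary outcome measures section, and resource use is indeed collected separately. The reading is plausible, but the sentence as published says something else. The two readings also lead to different analyses, so the text still has to be corrected.

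The reply is right to resist three stronger readings that a reader might infer.

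- *Quality of life is never analysed as an outcome.* The article does not support this. Quality of life is a secondary outcome, and the same section says "To analyze the secondary outcome measures the Student's t-test, the Mann-Whitney test or the Chi-square test will be used". The misassignment concerns the economic analysis only.
- *The whole economic result fails.* It does not. Direct costs have a source independent of the EuroQol, and cost per fall avoided is a legitimate analysis for a falls-prevention trial. The article does not show how large indirect costs would be. Participants are aged 70 or older, which may limit productivity losses, but it says little about informal care.
- *The absence of a QALY analysis is itself an error.* A condensed article may leave utilities, prices and economic methods to a fuller plan that is not shown. The article does not say that falls will be the only effect. A QALY is a recommended use of the data, and its absence is not the defect.

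**Conclusion.** The point holds in a limited form. The Statistical analyses section assigns the EuroQol to a construct that it does not measure and that the rest of the article does not give it. This is a wrong statement in the plan and does not depend on detail left out of the article. Its effect is that the indirect-cost component has no valid named source and a health effect is placed on the cost side.

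The damage is confined to that component of a secondary, economic analysis. Direct costs, a cost per fall prevented based on them, the between-group comparison of quality of life, the primary falls analysis and the sample size are not affected. No monetary size can be given, because the article contains no cost or utility figures.

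The conclusion rests on the sentence being meant as printed, and on the fact that the EQ-5D yields a health profile or utility and no record of resource use. If the sentence is a slip, the remedy is the same correction. It should be made before the economic analysis is run.

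**What to change.** Reconcile the Statistical analyses section with the Secondary outcome measures section, in four steps.

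1. Remove the EuroQol from the cost side.
2. Base costs on the resource-use items in Table 2 (health care use, medication, walking devices, house adjustments) multiplied by unit prices. Add the programme's own costs: the lessons, and the refunded travel and arranged transport described in the Discussion. These programme costs are not in Table 2 and must come from trial records.
3. Either name another source for indirect costs or state that they are not included.
4. Use the EQ-5D in the economic analysis only as an effect, for example as 12-month QALYs from the four scheduled measurements, reported alongside cost per fall prevented. The tariff and the handling of uncertainty can be left to the full analysis plan.

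The cost is a corrected paragraph and modest extra analysis work. No new participants or visits are needed. If a source for indirect costs is added, it means a few further questionnaire items; if indirect costs are dropped, the cost perspective is narrower and the report should say so.
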